## Study Procedure

**(A) Recruitment and randomization**

Explanation about the study will be provided to participants as attached in the information sheet of appendix 11 and eligible persons with PD and family caregivers will be requested to sign an informed consent prior to participation in the study. Data on social-demography will be compiled and baseline measurements of functionality mobility and QOL of PD patients, caregiver knowledge, burden and QoL will be conducted and analyzed to ensure the two groups are comparable at baseline. The participants will then be randomly allocated into either the experimental group or the control group using ‘sealed opaque envelope’ technique by health personnel blinded to the study.

## (B) Family caregiver training module and usual intervention

Table 5 highlights the content of experimental and control group training. The experimental group will receive a structured, comprehensive family caregiver-training program while the control group will receive usual intervention which normally consist of advice from treating medical officers and usual therapy program by rehabilitation professionals as necessary. The usual program consists of physiotherapy (functional training, strength and balance training) and occupational therapy (activities of daily living training and self-care). Both groups will receive the interventions on a weekly basis for 12 weeks and followed-up weekly to ensure compliance and monitor any arising problems or adverse effects.

Table 5 Intervention summary in experimental and usual intervention

| Characteristics | Family caregiver training module | Usual intervention |
| --- | --- | --- |
| Total duration | 60-90 minutes for overall module | 60-90 minutes |
| Delivered by | Family caregiver | Healthcare professionals |
| Content | Multidisciplinary approach; various perspective from neurologist, nurses, PT, OT, SLP, psychologist, dietitians. | Individualized and as referred by the neurologist based on problems arised |
| Location | Home based | Hospital based |
| Frequency | As needed for 12 weeks | Appointment based for 12 weeks |

## (C) Training for family caregiver in experimental group

Training module booklet containing a multi-component training materials will be provided to facilitate care at home and the content of the module consisting of multi-care physical and psychosocial tasks and guidance on health care for PD. Training sessions will be conducted by a group of multidisciplinary health care teams at the Physiotherapy Unit of UKMMC. Thereafter, family caregivers will be asked to demonstrate the components to proceed with the module at home. Experts from each component will decide if retraining session is necessary.

## (C) Measurement of outcomes

Outcomes will be evaluated at week 0, 12 and at 6-month follow up. Program sustainability will be assessed at a 6-month follow up by a blinded assessor**.** Summary of the study procedure is as attached in the Figure 6.

Will be excluded based on

exclusion criteria

Persons with PD and their family caregivers will be screened in medical rehabilitation department of UKMMC (n=36)

Eligible participants will be randomized based on simple random sampling (n=36) and baseline measurements will be taken

Assessment after 12th week (n=36, intention to treat approach)

Allocated to control group; usual intervention (n=18)

Allocated to experimental group; family caregiver- training program (n=18)

[figure not shown]

[figure not shown]

[figure not shown]

[figure not shown]

Results compilation and reporting

Sustainability assessment of outcomes after 6 months

1. Sustainability of effects based on clinical effects measured at week 12
2. Adherence, compliance, drop outs and adverse events.

Assessment of outcomes after 12th week

Functions and mobility measured using MDS-UPDRS and TUG respectively

QoL of patient and family caregivers measured using EQ-5D.

Caregiving burden measured using Zarith Burden Interview.

Knowledge of carer measured using adapted , translated and validated questionnaire

Figure 6 Flow Chart of Phase III

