## Sampling Method and Sample Size Estimation

Eligible persons with PD will be recruited using a non-probability purposive sampling method. Selected participants (persons with PD) will then be allocated into either the test group (family-training program) or the control group (usual intervention) using simple randomization method. Sample size is calculated using Gpower software version 3.1. This study will use 6x2 Mixed Model Anova with post hoc analysis using Bonferroni. Therefore F-test (ANOVA repeated measures, within-between interactions) is chosen in Gpower software. Study power is set at 95%, alpha set at 0.05 and effect size of 0.41 was chosen based on the effect sizes for the primary outcomes of clinical interest from the study by Bueno et al. (2017). Based on sample size calculation, a total of 18 participants are required. Hence a minimum of nine PD patients and nine family caregivers (n=18 per group) will be recruited in each group which makes it a total of 36 participants in this study. Dropouts are not considered because intention-to-treat analysis will be used and all participants who are enrolled at baseline will be included in the final analysis.

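### Simple randomisation of 18 patient-caregiver pairs does not deliver the promised minimum of nine per arm, and Figure 6 leaves the randomised unit and the place of baseline unclear

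*Protocol*

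**What the plan says.** In the Phase III section Sampling Method and Sample Size Estimation, the allocated unit is the patient: "Selected participants (persons with PD) will then be allocated into either the test group". The other arm follows in the same sentence: "the control group (usual intervention) using simple randomization method". The section then derives a total of 18 participants and sets the arm sizes: "Hence a minimum of nine PD patients and nine family caregivers (n=18 per group) will be recruited in each group". It gives the study total as 36.

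Figure 6, under (C) Measurement of outcomes, states the randomisation step as "Eligible participants will be randomized based on simple random sampling (n=36) and baseline measurements will be taken" and shows 18 people allocated to each arm.

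Section (A) Recruitment and randomization says that baseline measurements "will be conducted and analyzed to ensure the two groups are comparable at baseline". The next sentence says that the participants are then allocated by sealed opaque envelopes. It does not say whether those participants are patients, caregivers or pairs.

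The protocol describes no blocking, no stratification and no envelope set with a fixed number per arm.

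**The concern.** Simple randomisation leaves the arm sizes to chance, whereas a stated minimum per arm and a flow chart with fixed arms treat them as settled. At 18 pairs the gap is not academic: the minimum equals half the total, so any departure from an even split breaks it. Whoever prepares the envelopes must then either follow the stated method and usually miss the stated arm sizes, or force the arm sizes by an undescribed method.

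Two matters of wording in Figure 6 add to this. Its randomised units are 36 participants, although the text allocates persons with PD, and the unit of randomisation decides what N means in the analysis. Its box also mentions baseline after randomisation, the reverse of the order in section (A). That order matters here because the EQ-5D and the caregiver burden interview are the respondents' own answers, and a respondent who already knows the arm may answer differently.

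**Working it through.** **1. What N = 18 counts.** From the sample-size section: repeated-measures ANOVA, within-between interaction, effect size f = 0.41, alpha 0.05, power 95%. From (C) Measurement of outcomes: m = 3 visits (week 0, week 12, 6 months). There are k = 2 groups. The correlation between visits (ρ) and the sphericity correction are not stated; I assume ρ = 0.5 and no correction.

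- λ = f² · N · m / (1 − ρ) = 0.1681 × 18 × 3 / 0.5 = 18.15
- df1 = (k − 1)(m − 1) = 2; df2 = (N − k)(m − 1) = 32; critical F = 3.295
- Power = 96.2%, and N = 18 is the smallest even total that reaches 95%.

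The plan's figure is therefore reproduced, as 18 patients in total. One caregiver per patient makes 18 pairs and 36 people, or 9 + 9 = 18 people per arm.

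**2. Chance of the promised arm sizes.** Under 1:1 simple randomisation of 18 pairs, the number in one arm is Binomial(18, 0.5).

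- P(9:9) = C(18,9) / 2¹⁸ = 48,620 / 262,144 = 18.5%
- P(one arm below nine) = 1 − 0.185 = 81.5%
- P(11:7 or worse) = 126,008 / 262,144 = 48.1%
- P(12:6 or worse) = 62,360 / 262,144 = 23.8%
- P(13:5 or worse) = 25,232 / 262,144 = 9.6%

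**3. What it would take to keep simple randomisation.** The chance that both arms reach nine is 49.7% with 20 pairs, 84.8% with 24, 92.5% with 26 and 96.4% with 28. Honouring the minimum with simple randomisation therefore means recruiting well beyond 18 pairs.

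**4. Cost in power.** For a split a : (18 − a), the relative efficiency is 4a(18 − a)/18². I multiply λ by this and keep the degrees of freedom. The protocol does not give ρ, so a range is shown.

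| Split | Relative efficiency | Power, ρ = 0.3 | Power, ρ = 0.5 | Power, ρ = 0.7 |
| --- | --- | --- | --- | --- |
| 9:9 | 100% | 87.7% | 96.2% | 99.8% |
| 11:7 | 95.1% | 85.9% | 95.3% | 99.7% |
| 12:6 | 88.9% | 83.4% | 93.9% | 99.6% |
| 13:5 | 80.2% | 79.2% | 91.3% | 99.2% |

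The assumed correlation moves the level of power more than the imbalance does. Splits no worse than 11:7 cover 100 − 23.8 = 76.2% of draws and cost at most about 2 points at any of these correlations.

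**5. Unit and order.** The text allocates persons with PD. Figure 6 randomises 36 participants, and its screening box, also 36, names persons with PD and their family caregivers. The pilot recruits 10 pairs per group in its text and shows 40 people, 20 per arm, in Figure 5. Both figures thus count heads where the text counts patients or pairs. On order, section (A) measures and then allocates, while the Figure 6 box names randomisation first and joins baseline to it with a plain conjunction.

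**The case against.** The best defence is that little is wrong in substance. The text names persons with PD as those allocated, the 36 is explained as nine patients plus nine caregivers in each of two arms, and the pilot counts in the same way. A caregiver qualifies only as the main caregiver living with the patient, and Table 5 has the caregiver deliver the module at home. Staff would keep pairs together. Section (A) is explicit that baseline comes first, and a joint box in a flow chart does not fix a sequence. Moderate imbalance costs little power. Most of this stands.

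A reader might infer from Figure 6 that 36 individuals are to be randomised separately, so that about half of the pairs (18 × 18/35, or about 9 of 18) would be split between arms. The documents do not support that as the plan: the sample-size section allocates patients, and the arithmetic of 36 is a headcount. A reader might also infer that baseline will be taken after allocation; the explicit procedure text says otherwise. Nor does the protocol say that Hoehn-Yahr stage, already restricted to I and II, is prognostic for every outcome, so the absence of stratification is not an error in the plan.

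The defence does not answer the arm sizes. An envelope set holding nine of each allocation would give 9:9, but that is restricted randomisation, it is not described, and the protocol says simple. Nor does the word minimum help, because the total is set at 36 people, which leaves no room above nine pairs per arm.

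**Conclusion.** The stated allocation method and the stated arm sizes do not agree. With 18 pairs and 1:1 simple randomisation, the promised minimum is met in 18.5% of draws and missed in 81.5%. This result is exact and needs only the 18 pairs and an equal allocation chance.

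The statistical harm is modest. Under ρ = 0.5 and sphericity, which are assumptions that happen to reproduce N = 18, power drops from about 96% to 94% at 12:6 and 91% at 13:5; other correlations shift all three figures. The case for change rests on an unkept minimum and an unnamed unit, not on lost power.

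The label of 36 and the baseline wording in Figure 6 are points of clarity. They should be corrected together with the method, but they do not show that pairs will be split or that baseline will follow allocation.

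**What to change.** In the Phase III sections Sampling Method and Sample Size Estimation and (A) Recruitment and randomization, replace the simple-randomisation wording with, for example: *The patient-caregiver dyad is randomised as one unit, from an unstratified permuted-block list with varying block sizes totalling 18 dyads, nine per arm. Allocations are held in sequentially numbered sealed opaque envelopes, each opened only after all baseline measures of that dyad are complete.*

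Redraw Figure 6 in dyads (18 randomised, nine per arm), with the baseline box before the allocation box, and drop the term simple random sampling, which describes selection rather than allocation. Make the matching changes in the pilot text and Figure 5 (20 dyads, ten per arm).

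Stratification by Hoehn-Yahr stage is optional. With so few dyads, each stratum can end in an incomplete block, so stratified blocks would not guarantee 9:9. If it is chosen, the text should no longer promise exactly nine per arm.

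The cost is a new envelope list and a few sentences, with no added participants. The downside is slightly more predictable allocation, which the varying block sizes limit. The change must be made before the first envelope is opened.

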## Summative evaluation

All outcome assessment will be conducted by a blinded assessor at week 0, week 12 and at a 6-month follow up.

## ASSESSMENT OF THE CLINICAL EFFECTS OF THE MODULE USING OUTCOME MEASUREMENT TOOLS

Summative evaluation measures the clinical effect of the module as tabulated in Table 3 which summarizes the outcome measurement for each variable used for persons with PD and their family caregivers.

- - - 1. Mobility is measured using TUG. A chair will be placed on one end of the 3 meters (m) and a cone on the other end of 3m. Participants will be asked to stand and walk for 3m, turn around the cone, walk again and sit down. Stopwatch will be started as participants rises from the chair and will be stopped as participants sit down. TUG has excellent test- retest reliability among PD population with intraclass correlation coefficient (ICC) ranging from 0.80 (Huang et al. 2011) to 0.85 (Steffen & Senney, 2008). A study by Bennie et al. (2003) reported TUG has excellent inter rater and intra rater reliability of ICC of 0.99 and

0.98 respectively. A study by Foreman et al. (2011) reported that TUG has good construct validity for PD, area under the curve value ranging from 0.68 during “on” stage and 0.80 during “off” stage when compared to the contrast test, Functional Gait Assessment. The authors further reported TUG is responsive during both “on” and “off” period of PD. Scoring of TUG test is the time taken in seconds, (s) to complete one lap as instructed. Brusse et al. (2005) suggested the mean normative TUG test data for PD persons is

14.8s with a minimum of 4.85 seconds for minimal detectable change (Dal Bello-Haas et al. 2011).

- - - 1. Functions namely motor and non-motor functions will be evaluated using therapist rated MDS-UPDRS. MDS-UPDRS is a revision of UPDRS and has total four parts which will be administered by the therapist. Part I and II consist of 13 questions each evaluating non motor and motor experiences of daily living respectively. Part III consist of 18 questions of motor examination while part IV asks six questions on motor complications. All parts of MDS-UPDRS has 5 response option, ranging from 0 (normal) to 4 (severe).The higher total summed score indicates greater functional decline among PD persons. It takes only 30 minutes to administer the questionnaire (Shirley Ryan Ability Lab, 2022). MDS-UPDRS shows excellent reliability and concurrent validity as comparative fit index shows greater than or equal to 0.90 and high correlations (r=0.96) between the MDS-UPDRS and the original UPDRS Part III (Pal & Goetz, 2013).
      2. QoL of family caregivers and persons with PD will be assessed using EQ-5D, a standardized, non-disease-specific tool to measure health states (EuroQoL 1990). This questionnaire consists of 2 parts; the EQ-5D descriptive system and the EQ visual analogue scale (EQ VAS) (EuroQoL 2015). In this study, EQ- 5D-5L descriptive system with five levels of response for each dimensions will be used. The EQ-5D-5L consists of five questions and each question has a single digit response option and participants can only select any one option per question. Each question resembles one item of QoL namely; mobility, self-care, usual activities, pain/discomfort, and anxiety/depression. The selected digits for all five questions will combined into a five-digit number describing the participant’s health state. The five digit number of each EQ-5D-5L health states will then be entered into the EQ-5D-5L index value calculator to generate single index value known as health utility value based on specific value sets of respective country (Van Reenen & Janssen 2015). The utility score ranging between ‘0’ and ‘1’ represent death and perfect health respectively (Szende, Oppe & Devlin 2007). To date, utility value set for Asian country was only available for Japan and Thailand (EuroQol 2016; Szende, Oppe & Devlin 2007), hence Thailand value set of EQ-5D-5L will be used in this study ([name], 2013).

The second part of EQ-5D is a 20cm scale called EQ VAS, to assess the patient’s perceived health status. ‘X’ mark will be placed on the EQ VAS scale which has two endpoints labelled “worst health” and “best health”. The marked value will then be written in the available column of the scale (Van Reenen & Janssen 2015). English and Malay version of EQ-5D-5L is available to be used. EQ-5D has good convergent validity as there is strong associations between the EQ-5D and PDQ-39 or SF-36 subscores of both outcome measures for persons with PD (Schrag, 2000). Translated version of EQ-5D has satisfactory predictive validity and test retest reliability among generic Malaysian population with ICC ranging <0.01 to 0.92 and the spearman rank correlation coefficient value ranging from 0.61 to 0.86 (Varatharajan & Chen, 2012). Even though, a study by Luo and colleagues (2009) conducted in Singapore proved that EQ-5D is valid in PD person, this study will establish the validity and reliability of this instrument among Malaysian PD persons as highlighted in instrument design.

- - - 1. Burden of caregivers will be measured using ZBI, the Malay version. Family caregivers will be asked to specify the extent of burden during caregiving in the 22 items questionnaire. Scores range from never (score 0) to nearly always (score 4). Total scores will be obtained from summing the total score of all 22 items with a maximum score of

88. Greater the score indicate greater the burden and a score above 17 indicate high burden (Bedard et al, 2001). Reliability was good for all scales (ordinal alpha 0.89-0.95). A recent study by Shim, Ng and Drahman (2017) reported high internal consistency of

0.898 and area under the curve of 0.786 which indicates excellent reliability and validity respectively of Malay version of ZBI among Malaysian population.

- - - 1. Knowledge of caregiver questionnaire will be adapted, translated into Bahasa Malaysia and validated based on the study by Moore and Knowles, (2006). The questionnaire is expected to have 13 items with scoring of true or false for each item. All 13 items will be summed to produce a total score with higher score indicating higher level of knowledge.

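### The Timed Up and Go score comes from one lap with no practice or repeat provided for; averaging two or three laps is an optional, cheap precision gain of uncertain size

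*Protocol*

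**What the plan says.** In the section on assessing the clinical effects of the module with outcome measurement tools, the protocol describes the TUG course (stand, walk 3 m, turn round a cone, return, sit) and then the score: "Scoring of TUG test is the time taken in seconds, (s) to complete one lap as instructed". Nothing in the visible text provides a practice lap, a second timed lap or an average. The pilot section on outcome tools refers to this same description, so the rule covers both the pilot and the main trial.

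The same paragraph gives two kinds of reliability figure. For test-retest in the Parkinson's population it cites an "intraclass correlation coefficient (ICC) ranging from 0.80" to 0.85, and a mean and minimal detectable change (MDC) of "14.8s with a minimum of 4.85 seconds for minimal detectable change". It also cites a study that "reported TUG has excellent inter rater and intra rater reliability of ICC of 0.99 and" 0.98 respectively, without saying in which population.

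On size, the Phase III section on sampling method and sample size states: "Hence a minimum of nine PD patients and nine family caregivers (n=18 per group) will be recruited in each group". TUG is done by patients only, so the mobility comparison has nine per arm. Outcomes are taken at weeks 0 and 12 and at the 6-month follow-up.

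**The concern.** An MDC of 4.85 s on a mean of 14.8 s is a large measurement error: 4.85/14.8 = 33% of the mean. TUG is the only tool designated for mobility, and mobility is named in research question 5 and specific objective 5. With nine patients per arm and no allowance for dropout, any noise that can be removed cheaply is worth removing. One lap takes about 15 s, so one or two more are among the few ways to gain precision without recruiting more patients. What is at stake is the chance of seeing a real mobility effect, not bias: the single lap applies equally to both arms.

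**Working it through.** **The plan's sample size.** The protocol states "Therefore F-test (ANOVA repeated measures, within-between interactions) is chosen in Gpower software" and "Study power is set at 95%, alpha set at 0.05 and effect size of 0.41 was chosen". With 2 groups, m = 3 visits, and an assumed correlation of 0.5 and no sphericity correction, λ = N·m·f²/(1−ρ) = 18 × 3 × 0.41²/0.5 = 18.2 on 2 and 32 degrees of freedom. Power is 0.962, and 18 is the smallest even total reaching 95%. So 18 (nine per arm) is reproduced. The effect size is not expressed in TUG seconds, and TUG measurement error does not enter, so a better TUG score would not change the planned 18.

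**Measurement error implied by the protocol's figures.**
- SEM = MDC/(1.96·√2) = 4.85/2.772 = 1.75 s if the MDC is a 95% value. At the 90% level it is 2.08 s. The protocol does not say which.
- SD = SEM/√(1−ICC) = 1.75/√0.20 = 3.91 s, or 1.75/√0.15 = 4.52 s.

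**Change scores with one lap.** Variance = 2·SD²·(1−r), where r is the correlation between visits. The protocol gives no r. At an assumed r = 0.5 the variance equals SD², that is 15.3 to 20.4 s². This implies a true-change SD of √(SD² − 2·SEM²) = 3.0 to 3.8 s. At nine per arm, two-sided 5% and 80% power, the detectable standardised difference is 1.41. The detectable difference in change is therefore about 5.5 to 6.4 s (6.6 to 7.6 s with the 90% MDC).

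**Averaging k laps.** Let w be the lap-to-lap share of the error variance, an assumption throughout. Averaging removes 2·SEM²·w·(1−1/k) from the change variance. Because SEM²/SD² = 1−ICC, the MDC cancels from the relative gain:

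gain in effective sample size = 1/[1 − (1−ICC)·w·(1−1/k)/(1−r)] − 1

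Example with k = 3, w = 1, ICC 0.80, r = 0.5: 0.20 × 0.667/0.5 = 0.267, and 1/0.733 − 1 = 36%.

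| Lap-to-lap share w | Two laps | Three laps | Detectable difference, three laps |
|---|---|---|---|
| 10% | 2% | 2-3% | 5.4 to 6.3 s |
| 50% | 8-11% | 11-15% | 5.1 to 6.0 s |
| 100% | 18-25% | 25-36% | 4.7 to 5.7 s |

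(Ranges run over ICC 0.85 to 0.80 for the gains and 0.80 to 0.85 for the seconds; r = 0.5; 95% MDC.) On 18 patients the three-lap gain is worth 18 × 0.020 = 0.4 to 18 × 0.364 = 6.5 patients.

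**Sensitivity to r.** For three laps and w = 50%, the gain is 8-11% at r = 0.3 and 20-29% at r = 0.7. In the limiting case where every patient truly changes by the same amount, so that only measurement error remains, the detectable difference is 3.48 s with one lap. With three laps it is 2.84 s (w = 50%) or 2.01 s (w = 100%). If true change varies with an SD of 2 s and all error is lap-to-lap, power for a 2 s difference is 0.24, 0.32 and 0.37 with one, two and three laps.

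**The case against.** The strongest objection is that the deciding input is unknown. Repeats within a visit do nothing about day-to-day or on/off variation, and the quoted ICC and MDC do not separate these from lap-to-lap error. If the intra-rater ICC of 0.98 reflects repeat laps, the lap-to-lap share is about 0.02/0.20 = 10% to 0.02/0.15 = 13%, and the gain is only a few per cent. This stands. The reverse inference, that the rater ICCs prove lap-to-lap variation negligible, is not available either: they describe agreement between or within raters and are not stated to be from Parkinson's patients.

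It can also be said that one lap may define the course rather than the number of trials, and that the outcome tool in Appendix 10, which is not shown, may give a trial count. The course is already set out in the preceding sentences and the quoted sentence defines the score, so a single timed lap is the natural reading. But a reader who infers that the protocol rules out practice or repeat laps goes too far: the visible text is silent on both.

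The SD combines an MDC from one cited study with ICCs from two others, and the documents do not say whether those came from single or averaged laps. The figures in seconds are therefore approximate. The percentage gains avoid the MDC but still rest on the borrowed ICCs and the assumed r.

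Finally, TUG is not named as the primary outcome. MDS-UPDRS covers walking, balance and freezing, and EQ-5D has a mobility item. This limits the point's weight.

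**Conclusion.** The point holds as an optional, low-cost improvement in precision. As written, the TUG score is one lap with a standard error of measurement of about 1.75 s (2.1 s if the MDC is a 90% value), and no repeat is provided for. Averaging three laps would add between 2% and 36% to the effective sample size at a visit correlation of 0.5, depending almost wholly on a lap-to-lap share that the documents do not give.

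Two stronger readings are tempting and unsupported. One is that a single lap makes the mobility comparison invalid or biased; it is unbiased and equal across arms, and costs only precision. The other is that more laps would rescue the power of the comparison. Even if all the error were lap-to-lap, the detectable difference at r = 0.5 would still be about 4.7 to 5.7 s, roughly a third of the 14.8 s mean. The limiting factor is nine patients per arm, which this change does not address.

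**What to change.** State in the TUG description that at every TUG assessment, in both arms (weeks 0 and 12 of the pilot; weeks 0 and 12 and the 6-month follow-up of the main trial), the patient does one untimed practice lap and then two or three timed laps with a short rest. Fix the number of timed laps in advance, analyse their mean, and record each lap time.

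Keeping the individual times preserves a single-lap score for comparison with published values. It also lets the pilot supply the missing input: with 10 patients per group, two groups and two visits there would be 40 patient-visits if all attend. These would give 40 (two laps) or 80 (three laps) degrees of freedom for the lap-to-lap variance, which can be set against the pilot's own change-score variance before Phase III begins.

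The cost is one protocol sentence, extra fields on the case report form, about one more minute per patient per visit, and slight fatigue that is equal in both arms. No staff or equipment are added.
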